### The qualitative component

Some of the answers to questions (3) and (4) will be informed by the facility survey. As it may not be enough, we will complement our quantitative results with some qualitative information. Qualitative data collection activities are intended to explain the heterogeneity across facilities (treatment and control) in relation to all outcomes observed quantitatively. This should lead to a more comprehensive understanding of the underlying causes compared to what would otherwise be possible through an exclusive use of quantitative methods. In other words, the qualitative component is shaped in a way to fill the knowledge gaps identified by the quantitative components [19].

Not only will we try to understand how the changes occur but also why. By documenting regularly, throughout the intervention, all the events related to the prevention and management of malnutrition, we will be able to know the organizational changes resulting from the PBF and in particular the various strategies undertaken at the HCs to improve their performance. We will also conduct in-depth interviews (IDI) and focus group discussions (FGD) to understand the quantitative performance data. We will be particularly attentive to understand the reasons why the HCs from the intervention group did not perform better than in the ‘control’ group if this happens to be the case; why some have not adopted effective strategies adopted by their peers; why some are clearly better than others; why HCs underperforming failed to catch up with the best performing HCs.

#### Sampling

Sampling approaches for the qualitative study component differ from those in the quantitative components. Both HCs and respondents will be sampled purposively.

First, to identify the various strategies that could be taken by HCs throughout the intervention, we propose a prospective follow-up with logbooks, in all 90 HCs, which allow a weekly report on the events related to the fight against malnutrition.

Second, IDIs and FGDs will be carried out among HCs selected purposively within the intervention group depending on the patterns observed in nutrition PBF routine data of each HC throughout the intervention. We will consider HCs representative of each pattern and qualitative data collection will be carried out until we reach saturation. Respondents will be selected using maximum variation sampling for each HC (the staff of HC, users, other stakeholders of the system).

Third, IDIs and FGDs will be carried out among HCs selected purposively within each group (intervention and control) depending on the changes observed through the quantitative impact evaluation in nutrition performance. Within each group, two sub-groups will be represented: the better and the less performing ones. We will consider as a starting point the best and the worst performing HCs and qualitative data collection will continue until we reach saturation. As above, respondents will be selected using maximum variation sampling for each HC.

#### Data collection tools

##### Logbooks

Our first strategy is prospective and rests on the participation of HC managers in the study group (both treatment and control groups). They have been entrusted a paper logbook which allows them to record some basic information on (1) bottlenecks (e.g. a stock-out of nutritional inputs), (2) extra financial or in-kind assistance received (from technical and financial partners such as NGOs) and (3) initiatives taken by the HC staff to improve performance of the nutrition services (e.g. meeting with the CHWs to improve the retrieval of children lost in follow-up, photocopies of management tools not provided by the central level). The health managers are requested to document the nutrition activities, inside the health facility, among the CHWs, and around the HC on a weekly basis.

The aim of this tool is to document changes at these three levels in order to track their influence on the performance of the health facility. Filled logbooks are collected on a monthly basis. It is expected to be helpful background documentation for the retrospective qualitative interviews.

##### In-depth interviews with key informants

IDIs will be conducted among profiles such as HC managers, HC staff, district-and province-level stakeholders. An interview guide will be developed and tested on the basis of the different components of the theory of change and information reported in the logbooks.

##### Focus group discussions

Around the same HCs, FGDs among CHWs may be performed. An interview guide will also be developed and tested on the basis of the different components of the theory of change and the information reported in the logbooks.

#### Quality assurance plan and data management

Regarding logbook data, close monitoring is performed so that they are effectively filled in weekly. The collection of fulfilled logbooks is done monthly via the provincial committee (along with their verification activities) in sealed envelopes.

IDIs with key informants will be conducted following precise rules ensuring the quality of data collected (permanent reflexivity, flexibility in the selection and construction of data collection tools, awareness of social relationships and feelings, triangulation) and transcription (making quick notes and transcript). We will be conducting ourselves in-depth interviews in French. FGDs will be conducted in the local language with the help of trained research assistants.

All verbal material (IDIs and FGDs) will be tape-recorded, fully transcribed, and translated into French when necessary for analysis. Transcripts and translations will be checked for content consistency and accuracy.

#### Analysis strategy plan

For the prospective study using the logbooks, data will be evaluated regularly from the end of the first year with a final analysis after the final impact analysis. For the retrospective ones, IDIs and FGDs will be performed first, after the analysis of PBF routine data of 2015, and second, after the preliminary impact analysis. Data will be transcribed and uploaded in the software Nvivo. Transcripts from interviews and focus group discussions will be coded applying thematic content analysis, which identifies recurrent themes that form a cluster of linked categories containing similar meanings. Analyst triangulation will be applied across all qualitative data sets. An additional valuable source of triangulation will be provided by comparing findings across data sources and across respondents (policy stakeholders, providers, and users). Figure 3 below displays the main stages of this research.

## Discussion

This protocol relates to the measurement and understanding of the impact of an extension of the PBF program in Burundi to nutrition indicators.

This is an ambitious research project, by the multifactorial nature of the health problem addressed, the complexity of the intervention, the number of facilities participating and the set of international and national partners involved in the intervention and the evaluation. Moreover, there is today limited knowledge on how a PBF system addressing malnutrition should function, and the impact of the intervention is not guaranteed. By the date of submitting this paper (May 2016), we can report that this evaluation has to deal with three other unexpected challenges.

The first one relates to the incomplete clinic patient files and registers that could affect the power of ex-post calculation of the impact assessment at the HC level. To address this, we must advocate for good filling in and archiving of these files and registers.

A second limitation concerns the very low qualification of personnel. The critical issue here would be to enable (if possible) the HWs to attend training personalized to their needs, or at least to the needs identified for the HC as a whole. HCs managers formally expressed their demand for training and their willingness to pay for them, according to a Vickrey process: we plan to organise training for the HCs who showed most interest.

A third and final concern is obviously the political situation since April 2015 which has inevitably consequences on the health system. Indeed, some donors have already announced the cancellation of their budget support. We should also pay attention to donor decisions on the supply of inputs for the MAM.

This will be the first assessment of the extension of an existing PBF scheme to another set of indicators. The mixed methods design rests on the awareness that understanding the processes through which health interventions produce change is as important as measuring the actual change produced. It follows that a comprehensive assessment of health interventions can therefore only be achieved by coupling quantitative methods with qualitative ones as part of a systematic mixed methods study design [27].

Moreover, at this stage, no African country has yet applied PBF to malnutrition (at least systematically), while malnutrition is a huge problem in many poor countries. A growing number of them are in the process of conducting pilot PBF projects. If the evaluation leads to conclusive results about the introduction of nutritional indicators in the PBF program, such a strategy could attract many countries of the continent (or even beyond). To the extent that these countries are already advanced in their PBF experience, the introduction of nutrition indicators can benefit from extremely fast dissemination.

We hope that this explanatory mixed methods design will be able to contribute to existing evidence by addressing the current knowledge gaps related to the effect of PBF models specifically with respect to the adding of new indicators to an existing PBF scheme.

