### PBF extended to nutrition indicators

#### Design and roll-out of the PBF nutrition intervention

To tackle the challenge of malnutrition and provide malnourished children with the most appropriate care, the MoH decided in 2013 to add nutrition indicators to the existing PBF scheme. A systemic strategy being needed, it was decided to incentivise three levels of services: the district hospitals, the HCs and the CHWs, on both prevention and care aspects, with a focus on children below five years old.

The PBF indicators related to nutrition follow the standard model in Burundi, and come as a combination of quantitative indicators to encourage an increase in service delivery and coverage rates (see Table 1) and qualitative indicators to stress the importance of improving the quality of services to ensure a positive outcome for the user [18]. Quality of nutrition activities is assessed quarterly, and a bonus or penalty is applied to subsidies received by the facilities according to their quality score: a facility with a score above 80 % will receive a bonus equivalent to the score multiplied by 25 % of the nutrition PBF subsidies; while a facility with a score below 60 % will be subject to a penalty of 10 to 25 % of the nutrition PBF subsidies. The verification of activities related to nutrition PBF indicators is also included in the usual verification system (see above).

**Table 1 Tab1:** Quantitative indicators

Community level	(1) screening and referring of acute malnutrition cases to HCs, (2) organizing classes promoting good food and nutrition behaviours, and (3) organizing cooking practice classes.
Health centre level	(1) screening and caring severe and moderate acute malnutrition cases of children below five years old, or screening and referring acute malnutrition cases of children below five years old (depending on the type of HC^a^), and (2) growth follow-up and promotion for children below two years old.
Hospital level	(1) the number of treated severe acute malnutrition cases with medical complications of children below five years old and (2) the length of the stay at the hospital.

Note: ^a^Most of HCs do not provide care services for acute malnutrition cases and do have to refer cases to HCs that provide this type of care

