#### Theory of change

The introduction of nutrition activities into the PBF program translates policy makers’ belief that PBF can trigger some positive changes in the performance of the health personnel, facilities or system which will eventually impact on households and children. We have identified seven tracks for transmission of effects for the health facility performance:**The income track**: the injection of extra financial resources might have a positive effect on nutrition services, as it allows the health facility manager to recruit more staff, to better equip his facility, etc.**The cash track**: the fact that the financial resources are transferred directly to the health facility’s bank account allows the latter to rapidly and autonomously spend.**The incentive track**: the extra resources are conditioned upon higher performance in nutrition activities; this should motivate community actors and staff to improve their performance in order to boost the health facility’s income and theirs (if bonuses are distributed among HWs). At facility level, the effect on other services is unclear: it can be negative for some (e.g. if the staff in charge of nutrition used to be responsible for other services which are now overlooked, as they are relatively less financially rewarding) and positive for others (if there are economies of scope—i.e. dedicating efforts to nutrition activities, reduce efforts required for other activities, thanks to synergies).**The information track**: through the contract, the fee system and the related information sessions, staff have a clearer view on what performance should be, as far as nutrition services are concerned. Feedback from the program may also guide their decisions to improve. We hypothesize a positive effect on nutrition services. However, as for the incentive track, a negative effect could be that activities which are not remunerated may be perceived as non-important.**Supervision & enforcement track**: under the new scheme, verification is extended to nutrition activities; this means that there will be more interaction between supervisors and the personnel in charge of nutrition. On top of the possible subsequent transfer of information (e.g. advice on good practices), the supervision may activate interpersonal motivators.**Culture at provider level track**: a PBF scheme invites health facility managers to develop a work culture more favourable to innovation, flexibility, responsibility and entrepreneurship. As PBF has been a national policy for five years, one can assume that this is already the case in Burundi. However, one cannot exclude that it could positively influence the nutrition department more.**Health system track**: it has been argued that PBF can trigger several system effects [16]. Here, part of these effects might come from the supervisors of the impact evaluation (e.g. the MoH requesting UNICEF and the WFP to better supply nutrition inputs; the WB solving some problems which may affect the study). Another part might come from the health facilities themselves (e.g. pressure upon the Department for Nutrition within the MoH to be a more reliable and responsive supplier). We expect that CHWs will refer more malnourished children to HCs and HCs will refer more SAM children to referral hospitals. This may trigger some unexpected feedback loops.

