**Fig. 2 Fig2:**
[figure not shown]
Results chain of the introduction of nutrition criteria in the PBF grid

There is also a specific theory of change for the control HCs. The main design difference between the intervention and control groups is the formula to obtain the extra funding: each HC of the intervention group has to improve its own performance to increase its revenue; control HCs do not have any effort to do: they just have to hope that the intervention group, as a whole, will be performing. This choice for the definition of the two groups to compare indicates that the main causal path under investigation is the incentive one. Other tracks are not denied (see the qualitative part of the research) but are considered as secondary Table 2.

**Table 2 Tab2:** Routes applying in the Intervention and Control groups at the facility level

	Intervention group	Control group
(1) Income	++	++ ^a^
(2) Cash	++	++ ^a^
(3) Incentive	++ on nutrition services ? on other services	~
(4) Information	++	+ ^b^
(5) Supervision & enforcement	++	? ^c^
(6) Culture at provider level	~ or +	~ or + ^d^
(7) Health system	++	? ^e^

Notes: Symbols + and ++ mean that routes apply moderately to strongly; ? means unclear, ~ means neutral ^a^The control HCs will get additional financial resources which will correspond to a weighted average of the nutrition subsidies received in the intervention group. ^b^Before the start of the intervention, all 90 HCs were provided with some information on the nutrition indicators and on their performance in nutrition services. ^c^In a district where there are control and intervention HCs, the district team supervisors may transfer good practices to both intervention and control HCs. ^d^Control HCs know that there will probably be a scale up of the nutrition indicators to all HCs after the pilot; some managers may anticipate this by already reorganizing their nutrition services. ^e^Some health system effects might affect control HCs (e.g. if there is a problem of availability of nutritional inputs at national level, because of the pressure by intervention HCs, the supply to control HCs may be reduced)

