The sample size of clinical files within the HC survey was computed on the smallest difference in the main outcome that could be considered of public health significance in intervention centres. Assuming that the intervention will result in increasing the recovery rate of acute malnutrition in children under five years from 80 % to 90 %, for an α-error of 5 %, a power of 80 % and an inter-cluster correlation (ICC) of 0.15 [25], a minimum of 12 clinical files per HC and per nutrition service (MAM and SAM rehabilitation services) were needed, among all children having been registered in the six previous months [26].

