#### Data collection tools

The household survey focuses on question (1) and collects information on the nutritional and health status of each selected child, as well as general information on their household (including socio-economics, food security variables). The health facility survey focuses on questions (2), (3) and (4). To get information on malnutrition recovery rates, a total of 24 individual clinical files randomly selected among the files of all children below five years old enrolled in the MAM care program (12 files) and in the SAM care program (12 files) during the last six months are transcribed. In addition, organizational aspects of the HCs as well as of the nutrition services are recorded through interviews to managers. To assess the quality of services, we combine two techniques: patient-provider observations carried out on six paediatric consultations (performed by a maximum of two HWs) and exit interviews at the end of each of these observed consultations, in order to get information on the satisfaction level as well as to record anthropometrics of the children. Finally, to assess knowledge of the observed HWs, we use vignettes to measure the practical knowledge on different tasks to perform: a pattern of consultation is proposed and the health worker can ask all the questions (related to history and physical exams) necessary to arrive at a diagnosis and propose a treatment. Three vignettes are administered to every health worker observed in consultation.

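### Incomplete clinical files are described only as a threat to power, but if completeness depends on outcome and changes differently by arm, recovery read from those files is biased

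*Protocol article*

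**What the plan says.** Table 3 lists recovery rates and duration of treatment for MAM and SAM as the main outcomes at health-centre level. Under Data collection tools (quantitative component), recovery comes from 24 clinical files per centre, 12 MAM and 12 SAM, with the MAM files "randomly selected among the files of all children below five years old enrolled in the MAM care program" over the last six months. Sample size and randomization describes the base as files "among all children having been registered in the six previous months".

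The Discussion names as its first challenge "incomplete clinic patient files and registers that could affect the power of ex-post calculation of the impact assessment at the HC level". The response is that "we must advocate for good filling in and archiving of these files and registers".

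On what differs between arms:
- Design and roll-out of the PBF nutrition intervention: "The verification of activities related to nutrition PBF indicators is also included in the usual verification system", and "Quality of nutrition activities is assessed quarterly, and a bonus or penalty is applied to subsidies received by the facilities".
- Theory of change, supervision and enforcement track: "under the new scheme, verification is extended to nutrition activities".
- Theory of change, text on the control centres: "control HCs do not have any effort to do". Their compensation is a weighted average of what the intervention group earns.
- Table 2 rates supervision and enforcement as ++ in the intervention group and ? in the control group.

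**The concern.** Lost or unfinished files cost precision in either arm. They also select which children contribute an outcome, and the Discussion does not mention this. The files are kept by the centres under study. One group has its nutrition activities verified and scored for payment, and the other is paid without having to perform. How well files are completed could therefore be changed by the intervention itself.

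If children who did not recover are less likely to leave a usable file, recovery among usable files is too high. If that inflation differs by arm, the comparison is distorted: a real gain may be hidden, or an apparent gain may be an artefact.

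The described safeguards do not reach this. Pairing and the baseline comparison deal with differences that existed before the intervention. The quality assurance plan checks anthropometric accuracy and data entry, not whether a sampled child's file exists and shows an outcome.

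**Working it through.** **1. The plan's own figure.** Inputs from Sample size and randomization: recovery 80% versus 90%, α 5% (two-sided assumed), power 80%, ICC 0.15, 45 centres per arm.

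n per arm = [1.96·√(2·0.85·0.15) + 0.8416·√(0.8·0.2 + 0.9·0.1)]² / 0.10² = 199.

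With 12 files per centre the design effect is 1 + 11·0.15 = 2.65, so 199·2.65 = 527 files are needed and 45·12 = 540 are available. With 11 files the effective size is 198.0, just short of 199. The stated minimum of 12 is reproduced: effective size 540/2.65 = 203.8, power 80.9%.

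**2. The risk that the article names.** Fewer usable files per centre, lost at random:

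| Usable files per centre | Power |
|---|---|
| 12 | 80.9% |
| 10 | 78.5% |
| 8 | 74.9% |
| 6 | 69.3% |

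This loss is modest because the ICC is high.

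**3. The risk that it does not name.** Let p be true recovery, r the chance that a recovered child's file is usable, and u the same chance for an unrecovered child. Then

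observed recovery = p·r / [p·r + (1 − p)·u].

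The document gives neither r nor u, so all values below are assumptions. True recovery is 80% in both arms, so there is no effect.

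*Completeness unequal by arm but unrelated to outcome* (control 70%, intervention 95%): both arms show 80.0%, so the bias is 0.

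*Outcome-dependent loss in one arm only*, with r = 0.90 in that arm and completeness unrelated to outcome in the other:

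| u in the affected arm | Observed recovery there | False difference if control is affected | False difference if intervention is affected | Rejection rate of a nominal 5% test |
|---|---|---|---|---|
| 0.80 | 0.72/0.88 = 81.8% | −1.8 points | +1.8 points | 7.5% |
| 0.70 | 0.72/0.86 = 83.7% | −3.7 | +3.7 | 16% |
| 0.60 | 0.72/0.84 = 85.7% | −5.7 | +5.7 | 33% |
| 0.50 | 0.72/0.82 = 87.8% | −7.8 | +7.8 | 57% |

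Rejection rates use a normal approximation with 12 usable files in each of 45 centres per arm (effective size 203.8).

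*A true gain from 80% to 90%*, with control the affected arm and u = 0.80, 0.70 or 0.50, appears as 90.0 − 81.8 = 8.2, 90.0 − 83.7 = 6.3 or 90.0 − 87.8 = 2.2 points.

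**4. Would one common imputation settle it?** Take 80% true recovery in both arms. Intervention files are usable for 90% of recovered and 70% of unrecovered children, control files for 86% of both. The unusable share is 0.8·0.10 + 0.2·0.30 = 14% in intervention and 14% in control.

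- Unusable = not recovered in both arms: 72.0% versus 68.8%, difference +3.2.
- Unusable = recovered in both arms: 86.0% versus 82.8%, difference +3.2.
- Arm-specific bounds: 86.0 − 68.8 = +17.2, and 72.0 − 82.8 = −10.8.

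Agreement between the two common imputations can support a false effect. The arm-specific bounds contain the true difference of zero, but they are 28 points wide.

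**The case against.** A reader might infer that record-keeping is verified in one arm only, and hence that completeness will improve there. The document does not say so. It speaks of verifying activities. Restriction of nutrition verification to the intervention arm is a firm inference from the scheme's description, not a literal statement. Table 2 marks control as unclear, not absent. Its notes allow supervisors to carry good practice to control centres, report that all 90 centres were informed about the indicators, and allow control managers to reorganise in anticipation of scale-up. The advocacy in the Discussion is not limited to one arm, and better filing in both arms would help.

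Nor is there a documented incentive to tidy files so that they show a cure. Recovery is not a paid indicator in Table 1, and the contents of the quality score are not given.

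The two descriptions of the sampling base can be read as the same population. They diverge only when a registered child has no usable file, which the Discussion suggests may occur. Handling of missing outcomes may well sit in an analysis plan, and its absence from the article is not counted here. The Discussion sentence is also true as far as it goes.

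These objections limit the point but do not remove it. The article raises the problem itself and names only the consequence that more files could cure. Sampling from files is a design statement, and analysis cannot easily recover which children were never eligible to be drawn.

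**Conclusion.** The point stands as a credible risk of bias that the article leaves unnamed; a bias has not been shown. It needs two conditions together: completeness that depends on outcome, and a dependence that differs between arms. Unequal completeness alone produces no bias. The document fixes neither the size nor the direction. The range of about 2 to 8 points rests on assumed usability of 90% for recovered and 50 to 80% for unrecovered children in one arm, with outcome-independent completeness in the other. No single figure from that range should be read as an estimate, and a reader should not conclude that the intervention arm will look either better or worse. Against a planned difference of 10 points the range is large enough to act on before the follow-up survey.

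**What to change.** - **Sampling at follow-up.** Draw the 12 MAM and 12 SAM children from the enrolment register for the six-month window, then look for each child's file. Registers are also reported as incomplete, so supplement them with any other enrolment list. This reduces the problem without eliminating it.
- **No replacement.** Keep in the sample any child whose file is missing or lacks an outcome. Classify episodes still running at the survey separately, so that they are not counted as lost outcomes.
- **Reporting.** Give the unusable share by arm and by survey round.
- **Sensitivity analyses, not a rule for claiming an effect.** (a) Unusable = not recovered in both arms. (b) Arm-specific bounds: unusable = recovered in one arm and not recovered in the other, and the reverse.
- **Text.** Amend the Discussion to name possible differential bias as well as loss of power, and align the two descriptions of the sampling base.

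The cost is slightly more field work per centre and a few additional analyses. Some drawn children will have no treatment duration, and the arm-specific bounds may be wide where records are poor.
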